## Abstract

**Introduction::**

About 55% to 75% of stroke survivors have motor disorders and problems that affect their quality of life. The prevention of secondary neurological damages through relapse prevention and the rehabilitation of stroke patients suffering from morbidities are crucial to improve the prognosis of patients with stroke. Pulse examinations can be used to determine the stroke progression. This study will investigate the differences and changes in radial artery pressure-pulse waves during the treatment of hemiplegia caused by stroke.

**Methods/design::**

This study protocol is for a prospective matched case-control study. A total of 84 participants will be recruited, 56 patients with hemiplia caused by stroke, and 28 control patients matched by age, gender, and body mass index. The primary outcome of this study will be the differences and changes in the radial augmentation index.

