We will compare the pulse waves and hemodynamic characteristics of the affected and non-affected radial artery pulses in patients with stroke hemiplegia, and will assess the correlation between the brachial-ankle PWV (baPWV) and the blood viscosity to evaluate the stroke prognosis.

The aim of this study is to measure the pulse wave of the radial artery in stroke patients with hemiplegia, and to compare the changes in the pulse waves of the radial arteries on the affected and less affected sides of hemiplegic patients after rehabilitation by physiotheraphy, as well as to evaluate the effects of increased physical activities on the pulse wave of the radial artery (PWRA).

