### Study design

2.1

This study was conceived as a prospective and observational study to explore the differences and changes in radial artery pulse waves during the treatment of patients over 50 years old suffering from hemiplegia caused by stroke. As a matched case-control study, it aims to compare the pulse waves in the radial arteries of participants with hemiplegia caused by stroke with those of healthy participants. The study will be carried out at the Wonkwang University Gwangju Hospital Clinical Trial Center of Gwangju, in the Republic of Korea.

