### Data collection

2.5

The data will be collected through a participant survey and through investigator measurements at baseline (on visit 1) and at specified follow-up times (on visits 2 to 7). (Table 3)

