#### Primary outcome

2.7.1

Radial augmentation index (rAIx) The radial augmentation index (rAIx) measures the vascular compliance and stiffness of the radial arterial vessel walls, that is, the degree of variation in the magnitude of the pulse wave by the reflected wave. The radial augmentation will be calculated from the radial wave pulse as follows: (second peak SBP (SBP2) DBP)/(first peak SBP_DBP)_100,13, as shown in Figure 1.

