### Statistical analysis

2.8

The software package R (version 3.0.1, “R & R” of the Statistics Department of the University of Auckland, Auckland, New Zealand) or STATA version 13.1 (StataCorp, College Station, TX, USA) will be used for the statistical analyses. To ensure sensitivity analyses, analyses of the primary and secondary outcomes will be conducted on the full analysis set (FAS) and per protocol set (PP). The last observation carried forward (LOCF) method will be used to impute the missing data.

Baseline characteristics will be presented using the t-test or Wilcoxon rank-sum test for continuous outcomes, and the chi-square test or Fisher's exact test for categorical outcomes. The differences in the intergroup comparisons of the means will be processed with the least squared mean (LSM) and the standard deviation, and the intragroup comparisons of the mean values will be analyzed with a repeated-measures ANOVA (RMANOVA) or a linear mixed-effects model analysis (LME). *P* < 0.05 will be considered statistically significant. The time point difference in contrast with the baseline will be examined with Dunnett's test.

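### The primary outcome covers at least three unranked rAIx comparisons at P<0.05, so the chance of a false primary finding is about 14%, not 5%

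*Protocol article*

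**What the plan says.** The abstract (Methods/design) words the primary outcome as a plural: "The primary outcome of this study will be the differences and changes in the radial augmentation index". Section 2.7.1 (Primary outcome) defines the variable: "The radial augmentation index (rAIx) measures the vascular compliance and stiffness of the radial arterial vessel walls". It then gives the formula, but names no comparison, arm or time point.

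The aims point in different directions. The last paragraph of the Background sets out "to compare the changes in the pulse waves of the radial arteries on the affected and less affected sides of hemiplegic patients after rehabilitation". Section 2.1 (Study design) says of the study that "it aims to compare the pulse waves in the radial arteries of participants with hemiplegia caused by stroke with those of healthy participants". The same section also speaks of changes during treatment, and section 2.5 (Data collection) plans a baseline visit and follow-up at visits 2 to 7.

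Section 2.8 (Statistical analysis) lists between-group comparisons of means, within-group comparisons by repeated-measures ANOVA or a linear mixed model, and Dunnett's test for time points against baseline. Its general rule is that P "< 0.05 will be considered statistically significant". Primary and secondary outcomes are analysed in both the full analysis set (FAS) and the per protocol set (PP), introduced as sensitivity analyses.

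**The concern.** A primary outcome should say which single comparison decides the study, or how several share the error rate. Here the variable is fixed and the comparison is not. A significant result on any of the three routes could be reported as the primary finding, and nothing in the text would contradict that.

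Two things are at stake. First, the error rate of the headline claim is no longer the 5% that section 2.8 implies. Second, a mixed result has no agreed meaning: if cases differ from controls but the two sides do not differ, or the reverse, the document does not say whether the primary question was answered. This matters because the abstract and the Discussion both say the study will clarify whether the radial pulse wave can be used to judge the result of stroke treatment objectively.

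**Working it through.** **The plan's own figures.** The article states no error rate across comparisons. The figures that can be reproduced are the group sizes in section 2.4.4:

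- 47 / (1 − 0.15) = 55.3, rounded up to 56 cases
- 0.5 × 56 = 28 controls

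Both agree with the text.

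**Counting the families.**

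| Reading of the primary outcome | Source | Error control stated |
|---|---|---|
| Cases vs healthy controls | 2.1; between-group means in 2.8 | 0.05 |
| Affected vs less affected side | Background aim | 0.05 (general rule; no specific test named) |
| Change from baseline | Background, 2.1, 2.8 | 0.05 across visits, by Dunnett's test |

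Dunnett's test holds the whole set of visit contrasts in one series at 5%, so change over time counts as one family however many visits carry rAIx. No rule links the three rows.

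**Error rate, independent families.** P(at least one false positive) = 1 − (1 − 0.05)^k.

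- k = 1: 5%
- k = 2: 1 − 0.95² = 9.8%
- k = 3: 1 − 0.95³ = 14.3%

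Whatever the correlation, three families at 5% cannot exceed 3 × 0.05 = 15%.

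**Error rate, correlated families.** The three contrasts share data, so a normal-theory simulation under no effect was run with 400,000 draws per setting.

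- Inputs from the document: 47 cases, 24 controls (28 × 0.85 = 23.8, rounded up) and 7 visits.
- Assumed inputs: correlations of 0.3, 0.5 and 0.8 between arms and the same values between visits, and rAIx measured at every visit.
- The group and side contrasts were taken at baseline. The six change contrasts were taken in the affected arm, with their joint critical value set to give 5%.

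| Quantity | Result |
|---|---|
| Cases vs controls plus change over visits | 9.3% to 9.6% |
| All three families | 13.2% to 14.1% |

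Taking the side contrast as the difference between arms in change to the last visit, which is closer to the Background aim, leaves the three-family result within the same range.

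**The case against.** The strongest reply is that the study is observational and described as exploratory. Its sample size rests on a 10% margin of error, not on power for a primary test, so error control across comparisons matters less than in a confirmatory trial. That stands as a reason for a lower weight. It does not remove the point, because the article names a primary outcome, sets a threshold and promises an answer on clinical usefulness.

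A second reply is that this is a condensed article and an analysis plan may settle the visit, the lead analysis set and the testing order. Such details are not counted as missing here. What is visible is that the article itself states the primary outcome as a plural and gives different main comparisons in the Background and in section 2.1.

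A third reply is that section 2.8 names no test between sides, and that the aims speak of pulse waves in general, not of rAIx alone. This is fair: the side comparison as a primary rAIx test is inferred from the aims. With only the other two families the figure is just under 10%.

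A reader might infer more than the text supports:

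- **Six visits each tested at 0.05.** With unadjusted visits the three families would reach 26.8% to 28.2%, but section 2.8 assigns these contrasts to Dunnett's test. Six rAIx follow-ups also cannot be confirmed, as the schedule table is not shown.
- **Separate series for each arm and for the controls.** With Dunnett's test in place, counting five or seven such families gives about 18% to 21% or 24% to 28%. The article does not offer per-arm tests or change in controls as primary claims.
- **FAS and PP as two further chances.** They overlap heavily and are introduced as sensitivity analyses. What remains is only that the deciding set is not named.

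**Conclusion.** The point holds at a moderate level. As written, at least three rAIx comparisons can each be read as primary at P<0.05, with no order or adjustment between them. The chance of at least one false primary finding is about 14% instead of 5%: 14.3% if independent, and about 13% to 14% simulated.

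The figure rests on reading the side comparison as a primary rAIx question, on two-sided tests (sidedness is not stated), and on Dunnett's test holding the baseline contrasts at 5%. The simulated range also rests on the assumed correlations. The figure would be higher only if further per-arm or control-group series were also treated as primary, which the document does not state.

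**What to change.** In sections 2.7.1 and 2.8, do one of the following:

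1. Name one rAIx contrast as primary, giving the groups or arms compared, the visit, the FAS as the deciding set, and a two-sided level of 0.05. Label the other rAIx contrasts secondary, or test them in a fixed order after the primary.
2. Keep all three as primary with a Holm adjustment. The smallest of the three P values is then compared with 0.05/3 = 0.0167, the next with 0.05/2 = 0.025 and the last with 0.05, stopping at the first that fails. The change family should enter with its Dunnett-adjusted P value.

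The lead contrast is the sponsor's choice. One candidate is the within-patient side difference in rAIx change from baseline to the last visit, given the Background aim and the claim to novelty in the abstract's Conclusion and the Discussion. The matched case-control design is an argument for the group contrast instead. Under either option, state that the PP analysis is supportive only, and align the abstract's wording.

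The cost is a few sentences, with no extra patients or data. The downside is that the other rAIx contrasts lose primary status or, with Holm, the tests become somewhat stricter.

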**Discussion::**

The results of the study will help to determine the differences and changes in radial artery pressure-pulse waves during the treatment of hemiplegia caused by stroke. The findings will provide information about the physiological and hemodynamic mechanisms.

**Conclusion::**

This will be the first study to analyze the pulse wave of the radial artery (PWRA) on the affected side and on the normal side in stroke patients with hemiplegia. This study will clarify whether the radial artery pressure pulse wave can be used to evaluate the result of stroke treatment objectively. The results of the study will be available in February 2019. The version of the protocol is v1.6 written in March 7, 2016.

**Ethics and dissemination::**

Written informed consent will be obtained from all participants. This study has been approved by the Institutional Review Board (IRB) of Wonkwang University Gwangju Hospital, Gwangju, Republic of Korea (WKIRB-2016/8). The study findings will be published in peer-reviewed journals and presented at national and international conferences.

**Trial registration number::**

This trial was registered with the Clinical Research Information Service (CRIS) of the Korea National Institute of Health (NIH), Republic of Korea (KCT0002147).

## Background

1

About 55% to 75% of stroke survivors have motor disorders and problems that affect their quality of life.^[1]^ These patients often show motor disorders associated with hemiplegia that limit their physical activities. Stroke has a high rate of relapse and leads to serious morbidities, including motor disorders, gait abnormality, and speech disorders. Therefore, the prevention of secondary neurological damages through relapse prevention and the rehabilitation of stroke patients suffering from morbidities are crucial to improve the prognosis of patients with acute ischemic stroke.^[2]^

Accurate stroke diagnoses can be made with computed tomography and magnetic resonance imaging. However, the clinical applications of these medical imaging techniques are limited, as it is difficult to install the equipment and to obtain repeated measurements to monitor the progress of the treatment, and expensive examination fees are involved.^[3]^

The risk of stroke is proportional to the arterial stiffness. In the case of atherosclerosis, the arteries have reduced elasticity and increased arterial stiffness, arterial pulse wave velocity, and pulse pressure. The pulse wave velocity (PWV) is an independent predictor of cardiovascular disease mortality, and an important predictor of the risk of atherosclerosis. It is a relatively simple method to assess the changes in arteries, and has the advantage of being repeatable and noninvasive. PWV measurements can predict the onset of stroke or cardiovascular disease, which can help to select a more appropriate treatment.

Pulse examinations are closely associated with motor function improvement through rehabilitation and exercise therapy, and with changes in the blood flow.^[4–7]^ These blood flow changes can affect the pulse waves in the radial arteries. Therefore, pulse examinations can be used to determine the stroke progression.

The arterial pulse can be measured noninvasively in superficial arteries-such as the carotid, brachial, radial, and femoral arteries-using applanation tonometry. In Eastern medicine, doctors analyze not only the temporal, but also the spatial characteristics of the pulse waves in the left and right radial arteries to diagnose diseases and to assess the effectiveness of treatments.

We will compare the pulse waves and hemodynamic characteristics of the affected and non-affected radial artery pulses in patients with stroke hemiplegia, and will assess the correlation between the brachial-ankle PWV (baPWV) and the blood viscosity to evaluate the stroke prognosis.

The aim of this study is to measure the pulse wave of the radial artery in stroke patients with hemiplegia, and to compare the changes in the pulse waves of the radial arteries on the affected and less affected sides of hemiplegic patients after rehabilitation by physiotheraphy, as well as to evaluate the effects of increased physical activities on the pulse wave of the radial artery (PWRA).

## Methods

2

### Study design

2.1

This study was conceived as a prospective and observational study to explore the differences and changes in radial artery pulse waves during the treatment of patients over 50 years old suffering from hemiplegia caused by stroke. As a matched case-control study, it aims to compare the pulse waves in the radial arteries of participants with hemiplegia caused by stroke with those of healthy participants. The study will be carried out at the Wonkwang University Gwangju Hospital Clinical Trial Center of Gwangju, in the Republic of Korea.

### Study duration

2.2

The study period is from August 1, 2016 to December 15, 2018.

### Ethics statement and trial registration

2.3

The study protocol was approved by the Institutional Review Board of Wonkwang University Gwangju Hospital in Gwangju, Republic of Korea (WKIRB-2016/8), and is registered with the Clinical Research Information Service (CRIS) of the Korea National Institute of Health (NIH) in the Republic of Korea (KCT0002147), which is a WHO Registry Network registry. Written informed consent will be obtained from all participants, in accordance with the Declaration of Helsinki.

### Participants

2.4

A total of 84 participants will be enrolled in this matched case-control study. The cohort will comprise 56 patients with hemiplegia caused by stroke, and half the number of control patients matched by age, gender, and body mass index (BMI). The 56 participants with hemiplegia caused by stroke and the 28 healthy participants will be recruited through advertisements, and the 56 patients with stroke hemiplegia will be recruited among the outpatients or inpatients of the Wonkwang University Gwangju Hospital. Each participant will receive an explanation of the study procedure and will be asked to sign the consent form. The patients’ vital signs and relevant histories will be recorded.

#### Inclusion criteria

2.4.1

- Case group(1)Men and women over 50 years old.(2)Patients with stroke diagnosed by computed tomography (CT) or magnetic resonance imaging (MRI) scans for the first time.(3)Patients with a stroke experience within the past 6 months.(4)Patients who have required hospital treatment to treat an ischemic stroke.(5)Patients with a manual muscle testing (MMT) score of 4 or less.(6)Patients with scores of 24 or more in the Mini Mental State Examination-Korean version (MMSE-K) and with no cognitive functional disability.(7)Patients who understand and are willing to comply with all of the test procedures, and who participate in the clinical study voluntarily.(8)Patients who have signed and submitted a consent form for participation in the clinical study.

-Control group(1)Men and women over 50 years old.(2)Subjects who have not been diagnosed with strokes.(3)Subjects with an MMT score of 5.(4)Subjects with an MMSE-K score of 24 points or higher and no cognitive functional disability.(5)Subjects who understand and are willing to comply with all of the test procedures, and who participate in the clinical study voluntarily.(6)Subjects who have signed and submitted a consent form for participation in the clinical study.

#### Exclusion criteria

2.4.2

- Case group(1)Patients diagnosed with a hemorrhagic stroke through CT or MRI scans.(2)Patients whose pulse waves cannot be easily measured due to malformation of their blood vessels around the wrist or to bone fractures, or patients who cannot comply with the test procedure for other reasons.(3)Patients with serious organic diseases (cardiac disorders or lung, liver, or kidney diseases), or a history of a central nervous system or psychiatric disorder or of taking psychoactive drugs.(4)Patients with neurological disorders other than strokes.(5)Patients with a SBP < 90 mmHg or > 220 mmHg, and/or a DBP < 40 mmHg or > 130 mmHg.(6)Patients with severe musculoskeletal diseases from injury or rheumatic diseases.(7)Pregnant or nursing women.(8)Patients with implanted cardiac pacemakers and electronic devices.(9)Patients who show skin trouble around the electrode attachment region or side effects during the electrode attachment.(10)Patients who cannot comply with the stroke clinical pathway (CP) provided by the treatment institution.(11)Patients with an unstable heartbeat.(12)Patients with a history of drug or alcohol abuse.(13)Patients who have participated in other clinical trials in the past 3 months.(14)Patients who have an abnormal reaction to traditional Korean medicine or acupuncture.(15)Patients considered inappropriate for the clinical study by the research head or staff.

- Control group(1)Subjects whose pulse waves cannot be easily measured due to malformation of their blood vessels around the wrist or to bone fractures, or subjects who cannot comply with the test procedure for other reasons.(2)Subjects with serious organic diseases (cardiac disorders or lung, liver, or kidney diseases), or a history of a central nervous system or psychiatric disorder or of taking psychoactive drugs.(3)Subjects with severe musculoskeletal diseases from injury or rheumatic diseases.(4)Subjects with a SBP < 90 mmHg or > 220 mmHg, and/or a DBP < 40 mmHg or > 130 mmHg.(5)Pregnant or nursing women.(6)Subjects with implanted cardiac pacemakers or electronic devices.(7)Subjects who show skin trouble around the electrode attachment region or side effects during the electrode attachment.(8)Subjects with an unstable heartbeat.(9)Subjects with a history of drug or alcohol abuse.(10)Subjects who have participated in other clinical tests in the past 3 months.(11)Subjects considered inappropriate for the clinical study by the research head or staff.

#### Participant recruitment

2.4.3

The participants will be recruited through advertisements on hospital websites and on bulletin boards. They will be fully briefed on the study, including on the measuring methods and the procedures used. The subjects interested in participating will be guided through the informed consent process by the investigator on their first visit. Once their written consent is obtained, they will be screened using inclusion/exclusion criteria to determine their eligibility. If eligible, a physician will acquire the baseline data, and the clinical research coordinator will then schedule the study procedure. The participant recruitment will be stratified by age, gender, and BMI.

#### Sample size

2.4.4

The sample size calculation was based on the 2010 age (50 years or older) and gender distribution data provided by the Korean Statistical Information Service (kosis.kr). The incidence rates of obesity and stroke were estimated according to the National Nutrition Survey conducted and released in 2014. The stratification variables were as follows: age (A_1_: 50–69 years; A_2_: 70 years or older), gender (S_1_: male; S_2_: female), and obesity status (O_1_: BMI < 25 kg/m^2^, O_2_: BMI ≥ 25 kg/m^2^). A total of 8 cells (strata) were created based on combinations of the 3 variables. The frequencies of the stratification variables in each cell are shown in the table.

The Neyman allocation method was used, and the sample size was calculated with a confidence interval of 95% (α=0.05) and a margin of error of Є=10% following equation was used to calculate the total sample size and the sample size for each stratum:^[8]^ 

 

*N* refers to the total number of stroke patients in the corresponding age group, *N*_*i*_ to the size of the *i* stratum of the patient group, *n*_+_ to the sample size of the patient group, *p*_+_ to the population ratio of the *i* stratum, z_α/2_ to the top 100 (α/2)% quantile in a standard normal distribution, Є to the margin of error, and *n*_+*i*_ to the sample size of the *i* stratum, where *i* = 1, …,8 and *h* = 8. The standard deviation 
[figure not shown]
 of the population in each stratum was derived from the information.

The sample size of the patient group was calculated according to the level of significance and the margin of previously selected errors as *n*_+_ = 47. The final target sample size for the stroke patient group was 

, accounting for a 15% drop-out rate. (Table 1)

